#### Impact of future event scale (IFES):

The IFES [25] is a 24-item questionnaire to assess the frequency and avoidance of intrusive mental imagery for future events in the past week, using a 5 point Likert scale (0 = *not at all*, 4 = *very strong*). We administer the intrusion and avoidance subscales (15 items).

#### List of Threatening Events (LTE):

The LTE [93] is a 12-item questionnaire to assess experienced life events, participants indicate if the life event occurred (*yes/no).*

#### Dutch credibility and expectancy questionnaire (CEQ):

The CEQ [94] is a 6-item questionnaire to assess treatment credibility and treatment expectancy. Patients rate treatment credibility and -expectancy on a 9 point Likert scale (1 = *not at all*, 9 = *totally*). Expected levels of improvement are rated on a 0–100 VAS (0 = *no expected improvement*, 100 = *totally recovered*).

#### Working Alliance Inventory (WAI-12):

The WAI-12 [95, 96] is a 12-item questionnaire to assess working alliance, rated on a 5-point Likert Scale (1 = *(almost) never*, 5 = *always*).

#### Intolerance of Uncertainty Scale (IUS):

The IUS [97, 98] is a 12-item questionnaire to assess intolerance of uncertainty, using a 5-point Likert scale (1 = *not at all*, 5 = *totally*).

#### Anxiety Sensitivity Index (ASI):

The ASI [99, 100] is an 18-item questionnaire to assess anxiety sensitivity using a 5-point Likert scale (1 = *(almost) never*, 5 = *always*).

#### Penn State Worry Questionnaire (PSWQ):

The PSWQ [101, 102] is a 16-item questionnaire to assess worrying, using a 5-point Likert scale (1 = *not characteristic at all*, 5 = *very characteristic*).

#### De novo fear conditioning task:

Individual differences in fear extinction will be assessed with a differential fear conditioning computer task, including four phases: 1) habituation; 2) acquisition; using a scream as aversive stimulus [103]; 3) extinction; 4) generalization of extinction. Patients will be asked to rate their distress (phases 1–4) and scream expectancy (phases 2–4) [103–105]. More information on this task can be found in a pre-registration validating this task in a non-clinical sample (https://osf.io/axwyd).

### Clinician: predictors, mediators and moderators

#### Demographics and expertise:

Based on earlier studies [106, 107], we will assess age, gender, years of expertise, main profession, clinical orientation, and memberships of professional associations. Clinicians rate their own perceived skills compared to other clinicians on two 0–100 VASs (0 = *poorest*, 100 = *the best*).

#### Attitudes Toward Psychotherapy Treatment Manuals (ATPTM):

The ATPTM [108] is a 19-item questionnaire to assess clinician's attitudes towards psychotherapy treatment manuals, using a 5-point Likert scale (0 = *strongly disagree*, 4 = *strongly agree*).

#### Evidence-Based Practice Attitude Scale (EBPAS:

The EBPAS [109] is a 15-item questionnaire to assess clinician's attitudes towards evidence-based practice, using a 5-point Likert scale (0 = *strongly disagree*, 4 = *strongly agree*).

#### Credibility Scale (CS):

The CS [110] is a 5-item questionnaire to assess to what extent clinicians perceive the intervention as credible, using a 7-point Likert scale (1 = *not at all*, 7 = *extremely*).

#### Predicting Treatment Outcome Survey (PTOS):

The PTOS is a self-developed 9-item questionnaire to assess to what extent clinicians predict treatment outcome and whether treatment is suitable for a patient, based on a questionnaire developed by Van Minnen and colleagues [106].

#### Working Alliance Inventory (WAI-12):

The WAI-12 [95, 96] is a 12-item questionnaire to assess working alliance, rated on a 5-point Likert Scale (1 = *(almost) never*, 5 = *always*).

#### Optimal exposure:

A 2-item self-developed clinician-administered questionnaire will be used to assess if optimal exposure was hindered using a 7-point Likert scale (1 = *not hindered*, 7 = *severely hindered*) and reasons why optimal exposure could not take place (e.g. *COVID-19 measures, avoidance, illness, too difficult, other*).

#### Instruments goal 3: elucidate mechanisms of change of this novel approach (EMDR therapy + exposure therapy)

### Mental imagery

#### Imagery interview and questionnaire:

The imagery interview is used to assess mental imagery related to panic disorder during the case conceptualization session and the between treatments measurement (T2). It is structured and combines sections of the Waterloo Images and Memories Interview (WIMI) [111], the imagery interview by Boterhoven de Haan and colleagues [112] and the Memory Characteristics Questionnaire [113]. First, patients will be asked to choose which disorder-related memory and flashforward is most distressing. Next, they will be asked to describe the flashforward and memory, in as much detail as possible and rate the images’ qualities on several dimensions, such as vividness, sensory quality, complexity etc. using a 7-point Likert scale. Finally, credibility of the encapsulated belief statement that the mental image depicts is rated using a VAS scale (0 = not at all, 100 = extremely).

#### Instruments goal 4: assess cost-effectiveness of the new approach (EMDR therapy + exposure therapy)

### Quality of life and cost-effectiveness

#### EuroQol (EQ-5D):

The EQ-5D [114] is a widely used 5-item questionnaire to assess quality of life. Impairment on several factors (e.g., mobility, self-care, daily activities) is measured on a 5-point Likert scale (1 = *no impairment*, 5 = *extreme impairment*). Patients also rate their current health on a thermometer ranging from 0 (*worst health imaginable*) to 100 (*best health imaginable*).

#### Additional treatment: Treatment Inventory of Costs (TIC-P):

The TIC-P [115] is an 84-item questionnaire to assess medical consumption (16 items), productivity losses (11 items), and chronic diseases (2).

The EQ-5D will be assessed during baseline (T1), between-treatments (T2), post-treatments (T3) and follow-up measures (FU1, FU2) and the TIC-P will be assessed at baseline (T1) and follow-up measures (FU1, FU2).

### Data analysis

Data of all randomized participants will be analyzed on intent-to-treat basis as well as the completer sample. The primary outcomes (panic disorder symptomology) as well as secondary outcomes (tolerability and adherence) will be analyzed using a mixed regression model, using baseline scores as a covariate. This enables us to identify any fixed or random effects resulting from the treatments and changes over time. To analyze count date (e.g., drop-out, no show), Poisson or negative binomial regression will be used. Data analysis strategies for the secondary goals (goals 2–4) will be pre-registered in prior to analysis in Open Science Framework [52].

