## Background

Anxiety disorders are among the most common mental disorders, with about one out of 14 people meeting diagnostic criteria at any point of time [1]. These disorders comprise panic disorder, agoraphobia, social anxiety disorder, specific phobia, and generalized anxiety disorder. Their key elements are excessive fear in anticipation or the presence of the feared (innocuous) stimulus/stimuli and avoidance of disorder-related situations [2], which cause personal suffering and/or functional impairment [3]. Annual societal costs associated with anxiety-related disorders are estimated at about €74 billion in the European Union [4] and $42 billion in the United States [5].

Cognitive-behavioral therapy (CBT) is the psychological treatment of choice for anxiety disorders recommended in clinical guidelines [e.g., [6]], and it typically includes a combination of cognitive restructuring and behavioral (e.g., exposure) interventions [6, 7]. During exposure therapy, patients are systematically confronted with stimuli and situations associated with their anxiety disorder (e.g., bodily sensations in case of panic disorder), so that the patient learns that the anticipated feared outcome does not occur (e.g., having a heart attack) [8]. Meta-analyses have shown large effect sizes for CBT in anxiety disorders, especially when exposure strategies are used [9, 10].

A recent meta-analysis, however, shows that exposure-based CBT is moderately efficacious for anxiety disorders compared to other interventions when controlling for non-specific treatment or placebo (pill or psychological) effects [9]. There is substantial room for improvement for at least four reasons. First, about 25–30% of patients refuse to start exposure therapy, because they find it too aversive [11, 12]. Second, about 10–20% of patients drop out prematurely [12–14]. Third, although meta-analyses show substantial effect sizes for (exposure-based) CBT, the response rate (i.e., the percentage of patients showing significant clinical improvement) is around 50% [15]. Finally, little research has focused on relapse after (exposure-based) CBT [16–18], but recent findings suggest that it occurs in about 14% of cases [17]. Additionally, laboratory research has shown that even when exposure-based training is initially successful, learned fear can later return [19]. Taken together, these results underline the need for treatment optimization.

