## Goals of the current study:

The main goal of this multicenter Randomized Controlled Trial is to investigate whether EMDR therapy with exposure therapy, relative to supportive counseling with exposure therapy, improves treatment efficacy, tolerability, and adherence in patients with panic disorder. The primary outcome measures are panic-related symptoms. Secondary outcome measures are: tolerability of exposure therapy (initial avoidance, willingness to start exposure therapy, considered drop-out; no-show and drop-out), related symptomatology (generalized anxiety, depression) and functional impairment. We hypothesize that: (1) EMDR therapy will be more effective in reducing panic-related symptoms, compared to supportive counselling from baseline (T1) to between-treatments (T2). (2) EMDR therapy + exposure therapy will be more effective in reducing panic-related symptoms, compared to supportive counseling + exposure therapy at post-treatment (T3). (3) EMDR therapy will result in higher tolerability of exposure therapy (less initial avoidance, more willingness to start exposure therapy, less considered drop-out; less no-show and actual drop-out) compared to supportive counseling. We further hypothesize that: (4) EMDR therapy will be more effective in reducing related symptomatology (generalized anxiety, depression) and functional impairment, compared to supportive counseling from baseline (T1) to between-treatments (T2). And (5) EMDR therapy + exposure therapy will be more effective in reducing related symptomatology (generalized anxiety, depression) and personal suffering/functional impairment, compared to supportive counseling + exposure therapy at post-treatment (T3).

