### Recruitment

Participants will be recruited at two specialized treatment centers in the Netherlands: Mondriaan/PsyQ Academic Anxiety Center and Altrecht Academic Anxiety center. Clinicians refer patients who potentially meet inclusion criteria after a standard intake procedure. Potential participants are invited for an information session with the research assistant, who examines inclusion and exclusion criteria. After providing informed consent, baseline assessments (T1) will be made. Afterwards, participants are randomized to one of conditions (EMDR therapy + exposure therapy or supportive counseling + exposure therapy). Inclusion will continue until 50 panic disorder patients completed posttreatment (T3).

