### Randomization

After baseline measures (T1) participants are randomized to one of the two conditions by a research assistant who does not conduct assessments, using computerized randomization (REDCAP) [53, 54]. Stratified randomization will be used to reduce bias by treatment center [55], to guarantee a balanced distribution of participants across conditions.

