### Sample size

For the primary objectives of efficacy, tolerability, and adherence, the sample size was calculated using G*power 3.1 [56] using a 2 (groups) × 2 (time) repeated-measures ANOVA. Given the active control condition, we expect a medium effect size [9]. For a between group effect size of f = 0.25, alpha 0.05, power 0.80, 0.5 correlation among repeated measures and 1.0 non-sphericity correction, a total sample size of 98 participants is needed for two-sided testing. Although no formal method is available to determine a repeated-measures ANOVA sample size using Bayesian statistics, approximations for t-test are available [57]. For a one-sided *t*-test with a power of 0.80 and a Bayes factor of 3 (indicating evidence for the data coming from the alternative than the null hypothesis), 87 participants are needed and for a Bayes factor of 5, 99 participants are needed. Originally, we aimed to recruit 100 participants (see pre-registration: ISRCTN - ISRCTN29668369). However, the COVID-19 pandemic has seriously impacted the number of referrals of patients with panic disorder. To increase the feasibility of the study, we formulated directional hypotheses and decided to use one-sided testing, which reduces our sample size to 50 participants [58]. This change was approved by the ethical committee on February 8 2023. Participants who will not show up to therapy sessions in the first two weeks of treatment will be considered non-compliant and will be described as dropouts. Dropouts will not be excluded from intent to treat analyses, but will be replaced by additional participants to preserve statistical power. The completer sample size will be sufficient to address secondary objectives.

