### Early completion

Early completion is defined as: (1) a score of 0 on weekly assessment scores (General Anxiety Disorder (GAD 7) and Panic Disorder Severity Scale (PDSS-SR) (2) in case of EMDR therapy, a SUD of 0 for all targets part of the case conceptualization (3) and no avoidance on the behavioral avoidance task.

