**Adherence rates**							
Drop out and no-show	-	X	-	X	-	-	-

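### Drop-out is a yes/no status per patient, but the analysis section classes it as count data and gives it Poisson or negative binomial regression, whose model-based standard error is too large

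*Protocol article*

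**What the plan says.** The Data analysis section of the protocol article first assigns mixed regression to the primary outcomes and to tolerability and adherence. It then makes a specific provision: "To analyze count date (e.g., drop-out, no show), Poisson or negative binomial regression will be used". It lists no model terms and no variance estimator for this analysis. Only the strategies for goals 2 to 4 are deferred to a later pre-registration; adherence belongs to goal 1.

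Elsewhere drop-out is something a patient has or does not have. Under Sample size, participants who miss therapy sessions in the first two weeks "will be considered non-compliant and will be described as dropouts". Under Goals of the current study, hypothesis 3 predicts "less considered drop-out; less no-show and actual drop-out) compared to supportive counseling". Table 1 records "Drop out and no-show" in both treatment phases, under adherence rates. The abbreviation list contains mixed logistic regression, but the text shown never uses it.

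**The concern.** Poisson regression takes the variance of the outcome to equal its mean, mu. A 0/1 outcome has variance mu(1-mu), which is smaller. Default Poisson errors are therefore too wide for drop-out, and the other named model assumes at least as much variance. As written, neither option has the right variance for this outcome.

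Adherence is part of the main goal, and the Discussion calls attrition an important outcome measure. With about 50 patients the comparison of drop-out already has little power. A model that gives some of it away could make a real difference in retention look weaker than it is.

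**Working it through.** The article gives no figure for this analysis, so there is none to reproduce. The check compares the stated model with one that has the correct variance.

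**Inputs**
- Drop-out rate: the Background says "about 10–20% of patients drop out prematurely". No rate per arm is given; 30% is an assumption outside that range.
- Patients: 25 per arm, from the target of 50. Equal allocation is assumed; the Randomization section gives no ratio but uses stratification "to guarantee a balanced distribution of participants across conditions".
- Test: one-sided (Sample size section) at 5%.

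**Standard error of the log risk ratio, n per arm**
- Poisson, model-based: sqrt(1/(n p1) + 1/(n p2))
- Binomial, or Poisson with robust variance: sqrt((1-p1)/(n p1) + (1-p2)/(n p2))
- With a common rate p the ratio of the two is 1/sqrt(1-p), whatever n is.

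| Drop-out rates | Poisson | Binomial/robust | Excess |
|---|---|---|---|
| 10% in both arms | sqrt(2/2.5) = 0.894 | sqrt(1.8/2.5) = 0.849 | 5% |
| 20% in both arms | sqrt(2/5) = 0.632 | sqrt(1.6/5) = 0.566 | 12% |
| 20% vs 10% | sqrt(0.2 + 0.4) = 0.775 | sqrt(0.16 + 0.36) = 0.721 | 7% |
| 30% in both arms (assumed) | 0.516 | 0.432 | 20% |

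**Worked example: 5/25 vs 3/25 drop-outs (risk ratio 0.60)**
- Poisson SE: sqrt(1/5 + 1/3) = 0.730.
- Robust Poisson and log-binomial SE: sqrt(0.80/5 + 0.88/3) = 0.673.
- Pearson dispersion: (25 x 0.80 + 25 x 0.88)/48 = 0.875, below 1.
- The maximum-likelihood negative binomial dispersion goes to about 0, which returns the Poisson fit. Fixing it at 1 widens the SE to 0.783.

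**Size and power, by enumerating all outcomes of two binomials with n = 25, one-sided 5%**

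| Scenario | Poisson Wald | Logistic Wald | Poisson LRT | Binomial LRT |
|---|---|---|---|---|
| Size, 20% in both arms | 2.4% | 4.4% | – | 5.2% |
| Power, 20% vs 10% | 11.7% | 16.2% | – | – |
| Power, 30% vs 10% (assumed) | 37.9% | 48.0% | 51.8% | 57.3% |

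Part of the Wald gap comes from the change of scale from log risk to log odds. In simulation, robust Poisson, which changes only the variance, has power 14.8% at 20% vs 10% and 44.3% at 30% vs 10%.

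**The case against.** The strongest reply is that Poisson regression with robust variance is a valid model for a binary outcome and that the sentence does not exclude it. The variance estimator is the kind of detail an article leaves to the full plan, and the unused logistic abbreviation hints that such a model may exist there. This stands as a limit: the overstatement applies to model-based errors only. It does not remove the point, because the article does more than stay silent. It classes drop-out as a count and offers negative binomial regression as the alternative, which makes no sense for a 0/1 outcome.

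A second reply is that the effect is small and 25 per arm too few. Recruitment continues until 50 patients complete T3, dropouts are replaced, and all randomized patients are analysed. At 20% drop-out that is 50/0.8, about 62 randomized or 31 per arm. Wald power at 30% vs 10% is then 50.5% (Poisson) against 58.7% (logistic). Absolute power rises, and a gap of about 8 points remains. The SE ratio at a common rate does not depend on n.

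Two stronger readings are tempting, and the documents do not support them.

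- **Power falls from 57% to 38%.** A reader might infer this from the table, but it sets a Wald test against a likelihood-ratio test. Like for like the loss is about 10 points (Wald) or 5.5 (LRT), at a rate above the cited range. The binomial LRT is also no clean benchmark when events are few: its actual size is 7.5% at 10% drop-out and 5.7% at 15%.
- **No-show counts ignore the sessions each patient could miss.** The article lists no model terms, so it neither includes nor rules out an offset. One can construct a bias: if 30% vs 10% leave after 4 of 12 sessions, sessions at risk average 12 x 0.7 + 4 x 0.3 = 9.6 against 12 x 0.9 + 4 x 0.1 = 11.2, a ratio of 1.17 against the arm that retains more. Neither that timing nor a rule that missed sessions stop counting at drop-out is in the article. Since dropouts are described as patients who fail to attend early, the arm with more of them could equally show more no-shows. The passage beginning "Early completion is defined as" does not say what becomes of the remaining sessions.

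**Conclusion.** The point holds for drop-out. The article labels a per-patient yes/no outcome as count data and names two models whose model-based standard errors are too large for it: by about 5% to 12% at the cited 10–20% drop-out, and 20% at an assumed 30%. The direction is conservative relative to a binomial analysis. Some power is lost on one component of a secondary outcome, and no false positives are added. The power figures rest on 25 per arm, equal allocation, a one-sided 5% test and assumed rates per arm. They also show that drop-out is underpowered under any of these models, so the correction helps but does not rescue the comparison. For no-show, count regression is appropriate and no error is shown.

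**What to change.** Remove drop-out from the count-data sentence and state that it is analysed as a binary outcome. Use either logistic regression, penalised or exact if events are few, or log-link Poisson regression with robust variance. Report the risk difference with a 95% confidence interval, which will show how little about 50 patients can establish. Keep Poisson or negative binomial regression for no-show. When the full plan is written, an offset of log(sessions scheduled) would be a sensible addition, together with a rule for how sessions after drop-out or early completion are counted. The cost is one sentence in the analysis section, with no new data and no change to the conduct of the trial.

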## Discussion

We present a study protocol for the multicenter IMPROVE randomized controlled trial, examining whether EMDR therapy + exposure therapy vs. supportive counselling + exposure therapy improves treatment efficacy, tolerability, and adherence in patients with panic disorder. To our knowledge, this is the first study that specifically focusses on desensitizing future as well as past oriented threat-imagery, prior to exposure therapy. Furthermore, this randomized controlled trial will focus on theory-driven as well as non-specific patient and therapist factors predicting treatment outcome and optimal treatment allocation. By focusing on hypothesized underlying mechanisms of change and the long term effects of treatment we will broaden our understanding of treatment processes, potentially paving the way towards the era of personalized treatment. Lastly, cost-effectiveness of the new approach (EMDR therapy + exposure therapy) will be assessed when proven effective.

The study design has several strengths. First, a parsimonious principle was used in the development of the intervention by taking a mechanistic approach [116]. Instead of developing a new treatment, we aim to improve the best available treatment. As suggested by Clark [117], our research started with phenomenological observations [21, 22] followed by years of experimental research in our lab exploring the mechanisms involved [26, 46, 47], so our intervention is strongly grounded in theory as well as experimental research [42–44]. As a next step, we will now test the intervention in practice. Hereby, identifying predictors, mediators and moderators of treatment that could help us develop new theoretical models and aid diagnostic- and treatment decision-making [64, 116], paving the way into the era of personalized medicine [118].

Secondly, we expect to recruit a culturally and socioeconomically diverse sample. No strict exclusion criteria are used and clinics are in large cities across the Netherlands, which enhances the external validity of our results [119, 120]. Given that dropouts are common in this population [11–14], we will use an intention to treat analysis. Reasons for dropout will be monitored as attrition rates are an important outcome measure in this study. Validity of the trial is further improved by using standardized measures and by letting the assessments being conducted by researchers blind to treatment condition. Furthermore, the sample size should provide sufficient power for the primary- and secondary aims to enable meaningful conclusions.

Researcher allegiance bias is problematic in psychotherapy research [121, 122], including studies about EMDR therapy efficacy in anxiety disorders [38, 40]. Therefore, we follow recommendations to reduce research allegiance bias, such as having a collaborative team with mixed allegiances [121]. Study therapists are trained and supervised for the same amount of time for all treatment conditions, and treatment integrity will be checked [123]. To reduce expectancy biases in patients and clinicians a strong rational for all treatments, including supportive counselling, is provided. Furthermore, we use identical procedures (including EMDR-case conceptualization) and treatment duration between conditions. Treatment credibility and expectancy for all treatments are monitored for all patients and study-therapists.

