## Abstract

**Background:**

Exposure-based therapy is the treatment of choice for anxiety disorders, but many patients do not benefit sufficiently from it. Distressing images of threat related to the future or past may maintain the anxiety symptomatology or impede exposure therapy. An intervention that targets threat-related imagery is eye movement desensitization and reprocessing (EMDR) therapy. The main goal of this multicenter randomized controlled trial is to investigate whether EMDR therapy plus exposure therapy, relative to supportive counseling plus exposure therapy, improves treatment efficacy, tolerability, and adherence in patients with panic disorder. In addition, we will examine potential predictors of optimal treatment allocation, mechanisms of change as well as the long term effects of treatment. Finally, we will assess cost-effectiveness.

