Hypotheses concerning the following secondary goals will be preregistered on the Open Science Framework [52]. The first goal is to test whether EMDR therapy + exposure therapy results in less return of fear (panic related symptoms, generalized anxiety), compared to supportive counseling + exposure therapy from posttreatment (T3) to follow up (FU1 and FU2). The second goal is to unravel predictors of optimal treatment allocation (EMDR therapy + exposure therapy > supportive counseling + exposure therapy). These include theory-driven variables (reduced extinction learning, less experienced life events, low intolerance of uncertainty, anxiety sensitivity, low worrying, enhanced imagery ability), patient variables (e.g., greater treatment credibility, better working alliance) and therapist factors (e.g., enhanced trait anxiety, better working alliance, greater treatment expectancy). The third goal is to elucidate mechanisms of change (most notably mental threat imagery, encapsulated threat beliefs) of this novel approach (EMDR therapy + exposure therapy). Finally, we will assess cost-effectiveness of the new approach (EMDR therapy + exposure therapy).

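### Cost-effectiveness is an unconditional goal in the Abstract and the goals, but the Discussion makes it depend on an undefined proof of effectiveness

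*Protocol article*

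**What the plan says.** Three places in the protocol article set the aim without any condition:

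- Abstract, Background: "Finally, we will assess cost-effectiveness."
- Goals of the current study, last of the secondary goals: "Finally, we will assess cost-effectiveness of the new approach (EMDR therapy + exposure therapy)."
- Instruments, heading for goal 4: "Instruments goal 4: assess cost-effectiveness of the new approach (EMDR therapy + exposure therapy)."

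The schedule of economic measures is also unconditional. EQ-5D is taken at T1, T2, T3, FU1 and FU2, and "the TIC-P will be assessed at baseline (T1) and follow-up measures (FU1, FU2)." Neither is tied to the efficacy result.

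The first paragraph of the Discussion adds a condition: "Lastly, cost-effectiveness of the new approach (EMDR therapy + exposure therapy) will be assessed when proven effective." What would count as proof is not stated there or elsewhere in the article.

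The Data analysis section says: "Data analysis strategies for the secondary goals (goals 2–4) will be pre-registered in prior to analysis" on the Open Science Framework. It neither repeats nor lifts the condition.

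**The concern.** The article answers the question of whether the economic analysis will be done in two ways. Followed as the Discussion words it, the plan could leave goal 4 unanswered with the data already collected.

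The condition is also the wrong kind of rule. An economic evaluation estimates the difference in costs and the difference in effects together, with their uncertainty. It does not need a significant symptom difference to be informative. This design shows why. The two first-phase treatments are matched in number and length of sessions, and exposure therapy is common to both arms. Cost differences would therefore come largely from drop-out and no-show, early completion, additional treatment after FU1, and the medical consumption and productivity losses that the TIC-P records. Any of these could differ between arms without a significant difference in panic symptoms.

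Finally, the trigger is undefined and depends on the results. Table 1 lists five instruments under the primary outcome, and the hypotheses test efficacy at both T2 and T3. Which result opens the economic analysis could be settled after the results are seen.

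**Working it through.** **Inputs from the Sample size section.** "For a between group effect size of f = 0.25", alpha 0.05, power 0.80, correlation 0.5 between repeated measures, two groups and two times; N = 98 two-sided, later N = 50 one-sided. For two equal groups d = 2f = 0.5.

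**Assumptions of this check.** The condition is taken to mean one-sided p < 0.05 on one outcome, with 25 patients per arm. The article states neither. Recruitment continues until 50 patients complete T3, so the number randomised may be somewhat above 50.

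**Step 1: reproduce the plan's figure.** For the between-group test in a repeated-measures ANOVA with m = 2, the noncentrality is λ = f²·N·m / (1 + (m − 1)ρ).

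- N = 98: λ = 0.0625 × 98 × 2 / 1.5 = 8.17 on 1 and 96 df. Power is 0.808, and 98 is the smallest even N that reaches 0.80. The stated figure reproduces.
- N = 50, one-sided 0.05 (F test at 0.10): λ = 0.0625 × 50 × 2 / 1.5 = 4.17 on 1 and 48 df. Power is 0.64.

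A group-by-time interaction test with f = 0.25 would have power 0.97 at N = 50. That reading needs only 34 patients two-sided, so it is not the calculation that gave 98.

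**Step 2: standard error.** SE = √[(2/25) × (1 + 0.5)/2] = √0.06 = 0.245 SD. A single time point adjusted for baseline with correlation 0.5 gives the same value: √[(2/25) × (1 − 0.25)] = √0.06.

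**Step 3: how often the condition is met, and what it selects.** With a = 1.645 − d/SE:

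- P(met) = 1 − Φ(a)
- mean estimate given met = d + SE·φ(a)/(1 − Φ(a))

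| True effect (SD) | a | Analysis not run | Mean estimate if met | Ratio to truth |
|---|---|---|---|---|
| 0.2 | 0.83 | 80% | 0.54 | 2.7 |
| 0.3 | 0.42 | 66% | 0.565 | 1.88 |
| 0.5 | −0.40 | 35% | 0.638 | 1.28 |
| 0.8 | −1.62 | 5% | 0.828 | 1.03 |

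At 0.5 SD the normal approximation gives P(met) = 0.654, close to the 0.64 of step 1. With a single time point and no baseline adjustment, SE = √(2/25) = 0.283. At 0.5 SD the analysis is then not run in 45% of trials, and the ratio is 1.41.

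**Step 4: carry-over to the economic quantities.** At 0.5 SD the selected estimate moves up by (0.638 − 0.5)/0.245 = 0.56 SE. Under approximate normality, an estimate whose correlation with it is r moves by 0.56 × r of its own SE. The article gives no r. For assumed values of 0.2 to 0.6 the shift is 0.11 to 0.34 SE.

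**Step 5: effect of leaving the criterion open.** If success on any one of the five primary instruments sufficed, the chance of meeting the condition with no true effect would not be 5%. It would be 19%, 17% or 13% for assumed pairwise correlations of 0.3, 0.5 or 0.7 (simulation). A requirement of success on all five would be met less often than one on a single outcome.

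**The case against.** The strongest reply is that the condition is one closing sentence in a narrative summary. The Data analysis section defers the strategies for goals 2–4 to a pre-registration that is not at hand, and the trigger may be settled or removed there. This stands in part: how the economic analysis is done is properly left to that document. But the article itself says whether it is done, and says so in two ways. The deferral does not resolve that.

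Three stronger readings are tempting, and the documents support none of them.

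- A reader might infer that the article makes the analysis depend on a significance test. It does not say so. The one-sided, single-outcome criterion above is an assumption, and the result varies widely with it and with the true effect.
- A reader might infer that results would be reported only where the effect is overestimated. At a true effect of 0.5 SD the cut-off is 1.645 × 0.245 = 0.403 SD, below the truth. Of all trials, 0.654 − 0.500 = 0.154 would meet the condition with an underestimate, which is 0.154/0.654 = 24% of those that meet it. The estimate is inflated on average, not in every trial.
- A reader might take the 28% as bias in the cost-effectiveness result. It belongs to the triggering outcome. The goal 4 instruments are EQ-5D and TIC-P, for which the shift is smaller and unknown. The full figure would apply only if the triggering scale were also the effect measure, which the article does not state.

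It is also fair to say that little is at risk beyond goal 4. No clinical result is touched, and because data collection is unconditional, nothing is lost for good.

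**Conclusion.** The point holds as an internal contradiction joined to a poor and undefined rule. On the assumed criterion (one-sided p < 0.05, one outcome, 25 per arm, SE 0.245 SD), goal 4 would be left unanswered in about 35% of trials at the planned effect of 0.5 SD, with a range of about 5% at 0.8 SD to 80% at 0.2 SD. In trials that proceed, the triggering outcome's estimate averages 1.28 times the truth at 0.5 SD, and 1.03 to 2.7 times over the same range. The direction of any carry-over to EQ-5D or costs follows their correlation with that outcome, and its size cannot be derived from the article. Severity is modest: a secondary goal is affected and the primary analysis is not.

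**What to change.** Delete the final three words of the Discussion sentence, so that it agrees with the Abstract, the goals section and the goal 4 heading. In the pre-registration promised under Data analysis, state that the cost-effectiveness analysis will be run on all randomised patients whatever the clinical result, and that incremental costs and effects will be reported with their joint uncertainty.

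This changes neither the sample size nor the data collection. Whether goal 4 is analysed no longer depends on the efficacy result, and the selection disappears (expected estimate back from 0.64 to 0.50 SD at the planned effect). The only cost is analysis work that the goals already promise.
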